# A randomised controlled multicentre investigator-blinded clinical trial comparing efficacy and safety of surgery versus complex physical decongestive therapy for lipedema (LIPLEG)

**DOI:** 10.1186/s13063-021-05727-2

**Published:** 2021-10-30

**Keywords:** Lipedema, Complex decongestive therapy, Liposuction, Randomisation, Phase 3

## Abstract

**Background:**

Lipedema is a chronic disorder of the adipose tissue that affects mainly women, characterised by symmetrical, excessive fatty tissue on the legs and pain. Standard conservative treatment is long-term comprehensive decongestive therapy (CDT) to alleviate lipedema-related pain and to improve psychosocial well-being, mobility and physical activity. Patients may benefit from surgical removal of abnormally propagated adipose tissue by liposuction. The LIPLEG trial evaluates the efficacy and safety of liposuction compared to standard CDT.

**Methods/design:**

LIPLEG is a randomised controlled multicentre investigator-blinded trial. Women with lipedema (*n*=405) without previous liposuction will be allocated 2:1 to liposuction or CDT. The primary outcome of the trial is leg pain reduction by ≥2 points on a visual analogue scale ranging 0–10 at 12 months on CDT or post-completion of liposuction. Secondary outcomes include changes in leg pain severity, health-related quality of life, depression tendency, haematoma tendency, prevalence of oedema, modification physical therapy scope, body fat percentage, leg circumference and movement restriction.

The primary analysis bases on intention-to-treat. Success proportions are compared using the Mantel-Haenszel test stratified by lipedema stage at a 5% two-sided significance level. If this test is statistically significant, the equality of the response proportions in the separate strata is evaluated by Fisher’s exact test in a hierarchical test strategy.

**Discussion:**

LIPLEG assesses whether surgical treatment of lipedema is safe and effective to reduce pain and other lipedema-related health issues. The findings of this trial have the potential to change the standard of care in lipedema.

**Trial registration:**

ClinicalTrials.gov NCT04272827. Registered on February 14, 2020.

**Trial status:**

Protocol version is 02_0, December 17, 2019

**Supplementary Information:**

The online version contains supplementary material available at 10.1186/s13063-021-05727-2.

## Introduction

### Background

Lipedema was first described in 1940 by Allen and Hines [1] and has a registered diagnosis in the International Classification of Diseases [2] (ICD-10_GM Version 2020) coded stage-specifically (ICD10-E88.20, E88.21, E88.22, and E88.28). This disease, almost exclusively affecting females, is characterised by a symmetrical bilateral increase of the adipose tissue in the upper and/or lower extremities. It is unresponsive to physical activity or dietary intervention [3, 4]. A large proportion of the patients also shows the involvement of the arms [5]. Lipedema is associated with pain of the adipose tissue, increased touch sensitivity, feeling of tension in the affected regions and an increased tendency to haematoma after minor traumas [6]. Data on the prevalence of lipedema is limited. The prevalence of lipedema may be between 10 and 18% among women [7–9]. Child et al. estimated the prevalence within the female population as 1 in 72,000 [3]. However, lipedema is often misdiagnosed as obesity or lymphedema and therefore is incorrectly treated [3, 5]. Shivat et al. have established lipedema diagnostic algorithm to guide clinicians in making the correct diagnosis [10].

The aetiology of lipedema is unknown, but a genetic disposition is likely since lipedema is often seen in patients with a family history of this disease. X-linked dominant or gender-limiting autosomal dominant inheritance is assumed [3]. An important factor in the pathophysiology of lipedema is the increased capillary permeability, which leads to orthostatic edema and seems to be responsible for the increased tissue sensitivity in response to touch and pressure. Increased capillary fragility could explain the tendency towards haematoma formation [11].

The course of the disease is individual: some patients develop lipedema at a lower degree of severity and with stabilisation. Other patients show progression after stressful situations like pregnancy or surgery [12]. The onset of lipedema is common in teenage years, but is also observed after pregnancy or even menopause [3, 13].

Lipedema is divided into three stages according to skin morphology and palpation: stage I is characterised by smooth skin surface, thickened subcutis and small-nosed fat structure. In stage II, nodules appear in the fatty tissue and the skin surface is uneven, while in stage III, the tissue is hardened and rough with the presence of large deforming fat flaps [4].

The comprehensive decongestive therapy (CDT) is part of the standard conservative treatment [6]. Originally developed for the treatment of lymphedema, improvement has also been seen in patients with lipedema (reduction in leg circumference, tension, and pressure pain). As the treatment success is short-term, therapy is permanently necessary [4, 12].

CDT consists of a combination of lymphatic drainage, compression therapy (usually flat-knitted compression stockings), skin care and physical activity. It is unclear whether CDT influences the progression of pain in addition to the abovementioned benefits. However, the specific fat accumulation and distribution with the accompanying pain and tendency to form haematomas remain [5]. Physical activity, if necessary in combination with a dietary intervention, aims to reduce or prevent obesity, which has a negative prognostic influence on the development of lipedema [6, 10].

Starting in the 1990s, liposuction has emerged as the most important surgical intervention for lipedema. The pathologically altered subcutaneous fatty tissue is surgically removed without damaging the lymphatic system. Liposuction methods are tumescent anaesthesia (TA) and water-assisted liposuction (WAL). In TA, several litres of an anaesthetic solution are infused into the subcutaneous area (‘wet technique’) so that the fat cells swell and vessels constrict. Then, the subcutaneous fat is suctioned off by a very fine, blunt, vibrating cannula (power/vibration-assisted liposuction, PAL). In WAL, a jet of water releases the fat cells from the connective tissue and a mixture of fat cells, water and tumescent solution is aspirated [14–16]. This method is a tissue-friendly surgical method and minimises the risk of injuring vascular, lymphatic and nerve structures [4, 14, 17–19]. TA is standard for surgical treatment nowadays and recommended as the method of choice in the guidelines for lipedema [6].

Liposuction leads to reduction of lipedema-specific fat accumulation and distribution, pain sensitivity, edema, tendency to haematoma and restriction of movement [4, 19]. An improvement in the quality of life and a decrease in the need for conservative therapy has been shown [4, 11, 20–22].

Liposuction is therefore discussed as a useful addition to or even alternative therapy for CDT, especially in the early stages of lipedema in order to prevent possible long-term effects such as the development of secondary lymphedema and disease progression, to improve the quality of life and to reduce the need for CDT [4, 11, 20–22].

In summary, clinical experiences as well as small trials demonstrate a positive effect of liposuction in lipedema with respect to pain, movement improvement and quality of life. However, controlled and randomised clinical trials comparing conservative and surgical treatments with valid statistical methods are missing. There is no evidence that surgical treatment is equivalent or even superior to conservative treatment with respect to pain in lipedema stages I, II and III. Therefore, a large-scale randomised controlled investigator-blinded trial will be performed with the aim to provide a definitive answer.

### Rationale

Complex decongestive therapy is the standard of care for patients with lipedema. Liposuction is a non-standard alternative. The rationale of the LIPLEG trial is to compare effectiveness using leg pain reduction as the primary outcome in the two treatment groups.

### Objectives

The primary objective of the trial is to investigate whether the surgical treatment (treatment A) is superior to conservative treatment (treatment B) by comparing leg pain after 12 months. The secondary objective is to estimate the potential benefit of liposuction for the patient by evaluating changes in the severity of pain in the legs, health-related quality of life, depression and haematoma tendency, prevalence of edema, modification in the scope of conservative therapy, body fat percentage, leg circumference and movement restriction.

#### Primary outcome

The primary outcome is the reduction of pain in the legs 12 months after completion of liposuction or after 12 months of treatment by CDT upon randomisation, respectively (≥ 2 points on a numerical rating scale with range 0–10; German pain questionnaire).

#### Secondary outcomes

Change in the severity of the pain in the legsChange in health-related quality of life according to Short Form 36 (SF-36), Dermatology Life Quality Index (DLQI) and World Health Organization Quality of Life-abbreviated version of the WHOQOL 10 (WHOQOL-BREF)Altered depression tendency according to Patient Health Questionnaire-9 (PHQ-9)Altered haematoma tendencyPrevalence of edemaModification in the scope of physical therapyBody fat percentageChange of leg circumferenceReduction of the movement restriction (Lower Extremity Functional Scale, LEFS cumulative score)Occurrence of (serious) adverse events during the trial

### Trial design

LIPLEG is a multicentre, controlled, randomised, investigator-blinded trial. Female patients with lipedema interested in participating in the trial could register in an online portal until the end of December 2019. The patients are randomly drawn and assigned to a trial site according to the nearest post code. Then, the patients will be contacted by the trial sites and assessed for eligibility by telephone interview. If the patient is assessed as eligible, a screening visit on-site will take place in order to check the inclusion and exclusion criteria. Patients will be considered for enrolment when all inclusion criteria are confirmed, and none of the exclusion criteria is fulfilled. Four hundred five patients are planned to be included in the trial and assigned in a ratio of 2:1 to treatment group A (liposuction) or B (CDT). The investigator assessing the primary and secondary outcomes will be blinded. The surgeon, patients and further investigators will not be blinded for the allocated treatment. Since lipedema mainly affects females, males will not be included in the study.

## Methods

### Participants, interventions and outcomes

#### Study setting

The trial will be performed in > 10 trial sites in Germany, which are listed on ClinicalTrials.gov NCT04272827.

#### Trial sites

Only specialised trial sites (Dermatology or Plastic Surgery) are eligible for participation in the trial. Only principal investigators (PI) and participating trial sites that meet the necessary requirements, with qualifications and experience to conduct a clinical trial, are selected for the trial. Furthermore, only surgeons with sufficient experience in liposuction surgery can perform the liposuction in the trial. The sponsor designates the PI at each trial site, who selects qualified and experienced personnel to conduct the trial.

All trial sites will be trained during the initiation visit by the clinical research associate (CRA).

##### Eligibility criteria

*Inclusion criteria*
Signed informed consent formFemaleAge ≥18 yearsLipedema of the legs stages I, II or IIIAverage pain in the legs over the last 4 weeks ≥ 4 points on a numerical rating scaleDocumentation of an insufficient complaint relief by conservative methodsWillingness and ability to take conservative measures according to the study plan, during and, if necessary, after the liposuction treatmentFull legal capacity

*Exclusion criteria*
Simultaneous lipedema of the arms and legs in which the involvement of the arms influences the primary outcomePrevious liposuctionsDiseases affecting operability (e.g. cardiac diseases, coagulation disorders, metabolic diseases, body weight >120kg, active infectious diseases, epilepsy, diseases requiring immunosuppression or anticoagulation, allergies to drugs used before and during surgery)Diseases influencing adequate CDT, e.g. heart failure (volume stress), lack of physical ability to wear compression stockings (e.g. joint disease, neurological deficits).Primary obesity without disproportion and without reference to lipedemaSecondary obesityFat distribution disorders of other genesis (e.g. painless lipo-hypertrophy, benign symmetrical lipomatosis or lipomatosis dolorosa)Other edema causing diseases (e.g. lymphedema, phlebedema or myxedema)Lack of willingness to provide adequate contraceptionPositive pregnancy testLactation periodUsage of a lymphomatParticipation in other clinical trialsCosmetic motivation for participation in the trial

#### Interventions

In order to establish same starting conditions for all patients before randomisation, the trial participants initially receive CDT as recommended by the investigator in a run-in phase. The first part (phase I) of the run-in phase serves to eliminate edema within a maximum period of 4 weeks, followed by the second part (phase II), in which patients are treated with standardised CDT for a further 6 months to maintain the results achieved in phase I. Patients are then randomly assigned to one of the two treatment groups (treatment A: liposuction, treatment B: CDT) provided that all inclusion criteria are still met (and no exclusion criterion is fulfilled).

In the liposuction group, patients receive liposuction treatment using the wet technique. Techniques such as vibration (PAL) or water jet (WAL) can support the procedure depending on the amount of fat that is to be removed. A maximum of four surgical sessions is possible. CDT therapy is continued to the necessary extent for progression prophylaxis.

The CDT group is treated with CDT alone for further 12 months upon randomisation to maintain at least the results obtained at the end of the run-in phase. After this period, patients will be offered liposuction treatment provided all inclusion and exclusion criteria are still valid.

##### Study visits and assessments

A screening visit (baseline visit) on site will be performed by the investigator including written informed consent, check of inclusion and exclusion criteria, and medical history. The following parameters are recorded on the screening visit as well as on the subsequent visits: weight, supplementary medications, leg circumference, occurrence of leg edema, haematoma tendency, validated questionnaires for the determination of pain (German pain questionnaire), quality of life (SF-36, DLQI, WHOQOL-BREF), depression (PHQ-9), overall impairment modified according to Schmeller [23] and functional limitations (LEFS). All patients will then receive CDT during a run-in phase of maximal 7 months. After randomisation, the patients receive either liposuction and CDT in the following observation period of 36 months or CDT alone. After 12 months of observation, patients of the CDT group can opt for liposuction surgery followed by another 24 months of observation. During the trial, physical activities are permitted as an optional adjuvant treatment for lipedema. The supportive use of a lymphomat is not permitted during the trial. Compliance of patients with the trial procedures will be monitored by questionnaires and clinical examination during each study visit. Visits and assessments are described in more detail in Tables 1 (liposuction group) and 2 (CDT group). A detailed trial flowchart is shown in Fig. 1.

**Table 1 Tab1:** Visit schedule—liposuction group

Liposuction group		Run-in phase				12 months of observation		24 months of follow-up			
Visit	Screening *Day 0*	P1 *≤4 wks*	P2 *6 mo. after P1*		Lipo-suction(s) *1–4 mo. after P2*	V1 *6 mo.*	V2 *12 mo.*	V3 *6 mo.*	V4 *12 mo.*	V5 *18 mo.*	V6 *24 mo.*
						*After completion of liposuctions(s)*		*After V2*			
Informed consent	x			**Liposuction of the legs (2–4 surgeries at intervals of 5–7 weeks)**							
Information about liposuction	x				x						
In-/exclusion criteria	x		x								
Demographic data	x										
Anamnesis	x										
Concomitant medication	x	x	x		x	x	x	x	x	x	x
Weight	x	x	x			x	x	x	x	x	x
Leg circumference	x	x	x			x	x	x	x	x	x
Leg oedema	x	x	x			x	x	x	x	x	x
Body fat	x	x	x			x	x	x	x	x	x
Leg volume (optional)	x	x	x			x	x	x	x	x	x
Arm circumference	x	x	x			x	x	x	x	x	x
Skin appearance	x	x	x			x	x	x	x	x	x
Quality of life (SF-36, DLQI, WHOQOL-BREF)	x	x	x			x	x	x	x	x	x
Depression (PHQ-9)	x	x	x			x	x	x	x	x	x
Hematoma (mod. to Schmeller et al. 2010)	x	x	x			x	x	x	x	x	x
Overall impairment (mod. to Schmeller *et al*. 2010)	x	x	x			x	x	x	x	x	x
Pain (German Pain questionnaire)	x	x	x			x	x	x	x	x	x
Functional limitations (LEFS)	x	x	x			x	x	x	x	x	x
Randomisation			x								
ECG					x						
Laboratory data					x						
Pregnancy test	X		x		x						
Adverse events		x	x		x	x	x	x	x	x	x
Liposuction					x						
Query on the necessity of recurrent liposuction						x	x	x	x	x	x
Query on the scope of CDT	x	x	x		x	x	x	x	x	x	x

Abbreviations: *wks* weeks, *mo* months, *SF-36* Short Form 36, *DLQI* Dermatology Life Quality Index, *WHOQOL-BREF* World Health Organization Quality of Life-abbreviated version of the WHOQOL 100, *PHQ-9* Patient Health Questionnaire-9, *LEFS* Lower Extremity Functional Scale, *CDT* comprehensive decongestive therapy

**Table 2 Tab2:** Visit schedule—CDT group

CDT Group		Run-in phase		12 months of observation				24 months of follow-up			
Visit	Screening *Day 0*	P1 *≤4 wks.*	P2 *6 mo. after P1*	V1 *6 mo.*	V2 *12 mo.*		optional: Lipo-suction(s) 1-4 *mo. after V2*	V3 *6 mo.*	V4 *12 mo.*	V5 *18 mo.*	V6 *24 mo.*
				*After randomisation*				*After completion of liposuction(s) or V2*			
Informed consent	x					**On demand of the patient: liposuction of the legs (2–4 surgeries at intervals of 5–7 weeks)**					
Information about OP	x						x				
In-/exclusion criteria	x		x		x						
Demographic data	x										
Anamnesis	x										
Weight	x	x	x	x	x			x	x	x	x
Concomitant medication	x	x	x	x	x		x	x	x	x	x
Leg circumference	x	x	x	x	x			x	x	x	x
Leg oedema	x	x	x	x	x			x	x	x	x
Body fat	x	x	x	x	x			x	x	x	x
Leg volume (optional)	x	x	x	x	x			x	x	x	x
Arm circumference	x	x	x	x	x			x	x	x	x
Skin appearance°	x	x	x	x	x			x	x	x	x
Quality of life (SF-36, DLQI, WHOQOL-BREF)	x	x	x	x	x			x	x	x	x
Depression (PHQ-9)	x	x	x	x	x			x	x	x	x
Hematoma (mod. to Schmeller et al. 2010)	x	x	x	x	x			x	x	x	x
Overall impairment (mod. to Schmeller et al. 2010)	x	x	x	x	x			x	x	x	x
Pain (German Pain questionnaire)	x	x	x	x	x			x	x	x	x
Functional limitations (LEFS)	x	x	x	x	x			x	x	x	x
Randomisation			x								
ECG							x				
Laboratory data							x				
Pregnancy test	X				x		x				
Adverse events		x	x	x	x		x	x	x	x	x
Liposuction							x				
Query on the necessity of recurrent liposuction								x	x	x	x
Query on the scope of CDT	x	x	x	x	x		x	x	x	x	x

Abbreviations: *wks* weeks, *mo* months, *SF-36* Short Form 36, *DLQI* Dermatology Life Quality Index, *WHOQOL-BREF* World Health Organization Quality of Life-abbreviated version of the WHOQOL 100, *PHQ-9* Patient Health Questionnaire-9, *LEFS* Lower Extremity Functional Scale, *CDT* comprehensive decongestive therapy

**Fig. 1 Fig1:**
[figure not shown]
Trial flowchart. Abbreviations: *CDT* comprehensive decongestive therapy

##### Ancillary and post-trial care

For the optional ancillary treatment of lipedema, physical activities, especially water sports, are permitted, as recommended in the guidelines. However, the type and intensity of these should not be changed for the duration of the study. The supportive use of lymphomatics, on the other hand, is not permitted in the context of a desired homogeneous group of patients. After the end of the clinical trial, participants will be treated according to standard of care.

#### Withdrawal

Patients can withdraw at any time during the trial without providing a reason and without any personal disadvantage. A patient may also be withdrawn if, on the basis of the investigator’s judgement, continuation of the trial may be detrimental to the participant’s health. Further reasons for the investigator to discontinue a patient’s trial participation includes, e.g. insufficient compliance, patient becomes pregnant before reaching the primary outcome, inclusion and exclusion criteria are no longer met after the run-in phase. Reasons for all withdrawals will be recorded in the patient’s medical file and their electronic case report forms (eCRFs). All data will be analysed according to the intention-to-treat principle.

### Outcomes

#### Outcome measures and efficacy assessment

Efficacy assessments include the primary and secondary outcomes described above. The choice of these measuring instruments is based on the fact that lipedema has far-reaching effects on various socially relevant areas of the patient’s life that are covered by these measuring instruments.

Data will be recorded on eCRF. The primary outcome, pain in the legs, is collected either 12 months after the final liposuction surgery in the liposuction group or 12 months after randomisation in the CDT group by using the German Pain Questionnaire [24]. Occurrence of adverse events (AEs) and serious adverse event (SAEs) during the trial will be documented in the eCRF.

### Participant timeline

#### Proposed overall timescale

(see Supplementary Material)

### Sample size

#### Determination of trial size

According to the results of Schmeller et al. [22, 23], the success proportion of the intervention at each stage is expected to be at least 40% and that of the control to be at most 10%. The chi-square test requires 111 patients (74 vs. 37) per group to reach 80% power at two-sided significance level of 5% to detect such a difference. To compensate for the influence of dropouts and stratification, 135 patients per stage are included (this corresponds to an increase of approx. 20%). Accounting for up to 10% attrition from baseline to follow-up, the number of 450 patients is required in total.

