### Assignment of interventions

#### Patient randomisation

Patients are randomly assigned to the treatment groups (liposuction or CDT alone) centrally using the 24/7 Internet randomisation service ALEA (FormsVision BV, Abcoude, NL) in a 2:1 ratio (liposuction: CDT alone) based on permuted blocks of varying length as provided by ALEA using a pseudo-random number generator. Assignment is stratified by stage of lipedema and trial site. The randomisation service is set up and maintained by the Institute of Medical Statistics and Computational Biology, University of Cologne. Programming (using a web-interface) and validation of the service are done according to the Institute’s SOPs. The assignment of the groups can be made by all investigators, except the investigator (blinded investigator) carrying out the clinical assessments and questionnaires after surgery who should not be aware of who is receiving liposuction or CDT. The randomisation sequence is concealed from all clinical staff, i.e. only ALEA service administrators have access to the sequence.

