### Statistical methods

The primary analysis is according to the intention-to-treat. The primary outcome ‘success’ is evaluated by the stratified (by stage) Mantel-Haenszel test [25] at two-sided significance level of 5% (H_0_: odds ratio = 1 vs. H_A_: odds ratio ≠ 1). If this test is statistically significant, the equality of the success rates in the separate stages is evaluated by Fisher’s exact test (hierarchical test strategy). A missing primary outcome or change of the randomly assigned treatment is counted as failure. No interim analysis is planned. Secondary is the analysis of patients treated and observed per protocol (i.e. completed liposuction or ≥80% of planned CDT sessions done; valid primary outcome). Secondary and further outcomes are evaluated without adjusting for multiple hypothesis testing (i.e. no alpha correction is applied). Distributions of quantitative variables are described as mean (standard deviation) and percentiles (0, 25, 50, 75, 100), qualitative variables are summarised by count and percentage. The impact of missing outcome data is assessed by sensitivity analyses based on single/multiple imputation. The information on AEs is assessed (according to severity, intensity of symptoms, causal relationship to the CDT or intervention), coded and summarised by contingency tables. Subgroup analysis is done by patient age, study centre and surgeon.

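### The stated 80% power does not belong to 74 vs 37 patients: that size gives 90–94% power for 40% vs 10%, and 111 is a number per stage, not per group

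*Protocol article*

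**What the plan says.** Under *Determination of trial size*, the success proportions in each stage are "expected to be at least 40% and that of the control to be at most 10"%. The size follows: "The chi-square test requires 111 patients (74 vs. 37) per group to reach 80% power at two-sided significance level of 5"%. The next sentence inflates this figure and changes the unit: "135 patients per stage are included (this corresponds to an increase of approx. 20"%). *Patient randomisation* sets the allocation "in a 2:1 ratio (liposuction: CDT alone").

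The tests are given under *Statistical methods*. The primary test is a Mantel-Haenszel test stratified by stage. If it is significant, "the equality of the success rates in the separate stages is evaluated by Fisher’s exact test (hierarchical test strategy").

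**The concern.** Effect, level, power and size are tied by one formula, so three of them fix the fourth. Here all four are printed and they disagree. The paragraph is also the only justification of the trial size in the document.

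A reader who takes it at face value concludes that 80% power for 40% vs 10% needs 111 patients per stage. That reader would also accept a 20% chance of missing the assumed effect within a stage, when the true chance is well below that. This matters because the stage-wise tests belong to the hierarchical strategy, and a non-significant stage would be read against the wrong figure.

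The unit adds to the confusion: in a two-arm trial, *per group* normally means per treatment arm.

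**Working it through.** **Inputs, all from the protocol article.** Control p₁ = 0.10 and liposuction p₂ = 0.40 (*Determination of trial size*); two-sided α = 0.05, so z = 1.960 (same section); allocation r = 2 (*Patient randomisation*). z for power is 0.8416 at 80% and 1.2816 at 90%.

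**1. Size needed.** For the chi-square test with unequal allocation (Fleiss), the control-arm size is

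m = [z_α √((r+1) p̄ q̄) + z_β √(r p₁q₁ + p₂q₂)]² / [r (p₂ − p₁)²]

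with p̄ = (0.10 + 2 × 0.40)/3 = 0.30 and q̄ = 0.70.

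- First term: 1.960 × √(3 × 0.21) = 1.5557.
- Second term at 80% power: 0.8416 × √(2 × 0.09 + 0.24) = 0.5454. At 90% power: 1.2816 × 0.6481 = 0.8305.
- Denominator: 2 × 0.30² = 0.18.

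The continuity-corrected size is m_c = (m/4) [1 + √(1 + 2(r+1)/(m r |p₂ − p₁|))]².

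| Power | Correction | Control n | Rounded | Liposuction vs CDT | Total per stage |
|---|---|---|---|---|---|
| 80% | no | 2.1011²/0.18 = 24.5 | 25 | 50 vs 25 | 75 |
| 80% | yes | 29.3 | 30 | 60 vs 30 | 90 |
| 90% | no | 2.3862²/0.18 = 31.6 | 32 | 64 vs 32 | 96 |
| 90% | yes | 36.5 | 37 | 74 vs 37 | **111** |

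The plan's 111 is not reached at 80% power. It is matched exactly at 90% with continuity correction.

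**2. Power at 74 vs 37.**

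- Standard error under H₀: √(0.21 × (1/37 + 1/74)) = 0.09227.
- Standard error under H_A: √(0.09/37 + 0.24/74) = 0.07534.
- Uncorrected: z = (0.300 − 1.960 × 0.09227)/0.07534 = 1.582, power 94.3%.
- Corrected: the difference falls by ½(1/37 + 1/74) = 0.0203 to 0.2797, so z = 1.313, power 90.5%.
- Exact binomial enumeration: Pearson 94.6%, Yates 91.4%, Fisher 93.3%.

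The gap to the stated 80% is about 10 to 15 percentage points. Against 10% in the control arm, 80% power at this size corresponds to about 33–34% under liposuction without correction (33% gives 78.6%, 34% gives 81.7%). With correction it is about 36% (80.4%).

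**3. Other routes to 111 at 80% power** (uncorrected/corrected totals per stage):

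- one-sided 5%: 60/72
- 1:1 allocation: 64/76
- α = 0.025: 93/105
- α = 0.05/3: 102/117
- joint 80% over three stages by the chi-square formula: 105/120
- α = 0.01 without correction: 114, which is close but contradicts the stated 5%

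One-sided 5% at 95% power with correction also gives 111, but it contradicts both the stated sidedness and the stated power.

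**4. The unit.** 74 + 37 = 111 sums both arms. 135/111 = 1.216, the announced increase of about 20%, is expressed per stage, and 3 × 135 = 405 is the total in the abstract and under *Trial design*. So 111 is per stage. With 111 in each arm, power would be above 99.9% and the 74 vs 37 split would have no meaning.

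**5. Power of the planned tests at 135 per stage (90 vs 45).**

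- Chi-square, uncorrected: 97.7%.
- Fisher, exact: 97.4%.
- Fisher with 10% missing in both arms counted as failure, so 0.9 × 40% = 36% vs 0.9 × 10% = 9%: 95.1%.
- Mantel-Haenszel over all stages, approximated by 270 vs 135 with equal proportions in each stage: above 99.9%.

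**The case against.** The strongest objection is that another reading keeps the 80%. The stage-wise test is Fisher's exact test in three stages. If the aim was an 80% chance that all three succeed, Fisher power at 74 vs 37 is 0.933 and 0.933³ = 0.813, while at 72 vs 36 it is 0.924 and 0.924³ = 0.789. So 74 vs 37 just clears 80% and the next smaller 2:1 size does not. The arithmetic is right. But the sample size paragraph names the chi-square test and mentions no joint criterion, so the sentence as printed would still be wrong. What stands is that the origin of 111 is an inference on either reading, and only the sponsor can settle it.

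Three further objections:

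- *The unit is a slip that the context resolves.* True: the split and the next sentence show what is meant. It is still the wrong word and should be changed in the same edit.
- *Sizing by stage rather than for the Mantel-Haenszel test is legitimate.* This stands. It is a stricter choice, not an error. The primary test's power is worth stating, but its absence is a side point.
- *The discrepancy is conservative and harms nothing in the conduct.* This also stands, and it bears on how serious the point is. It does not make the power statement correct.

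**Conclusion.** The concern holds. From the stated inputs, 80% power needs 75 to 90 patients per stage, and the printed 111 has 90.5% to 94.6% power over the chi-square variants and 93.3% with Fisher's test. At a target of 80% per stage, the total before inflation would be 3 × 75 = 225 to 3 × 90 = 270, not 3 × 111 = 333. That comparison assumes each stage is powered separately, as the paragraph reads. The chance of missing the assumed effect within a stage is about 7% at 74 vs 37 and under 3% at 90 vs 45 (Fisher), not 20%.

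The trial is not underpowered by this error, and allocation, tests and significance level are unaffected. All figures rest on true proportions of exactly 40% and 10%; a larger difference would raise the power further. That 90% with continuity correction was intended is the simplest explanation of an exact match, but it is not documented.

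**What to change.** Rewrite the paragraph under *Determination of trial size*:

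- State that 111 patients per stage (74 liposuction, 37 CDT) give 90% power for 40% vs 10% with the continuity-corrected chi-square test at two-sided 5%, and 94% without the correction. This is true of 74 vs 37 whatever was originally intended.
- Replace *per group* by *per stage*.
- Add the power of the planned tests at 135 per stage: Fisher about 97% in each stage, about 95% if 10% are missing and counted as failures, and Mantel-Haenszel above 99.9%.
- Have the sponsor confirm how 111 was derived. If a joint criterion over the three stages was the basis, name that criterion and the test used.

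The cost is the correction of one paragraph. No patient numbers, tests or analyses change.
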